## Abstract

**Background:**

Unfractionated heparin is the most common anticoagulant used in haemodialysis (HD), although it has many potential adverse effects. Citrate dialysate (CD) has an anticoagulant effect which may allow reduction in cumulative heparin dose (CHD) compared to standard acetate dialysate (AD).

**Methods:**

This double-blinded, randomised, cross-over trial of chronic haemodialysis patients determines if CD allows reduction in CHD during HD compared with AD. After enrolment, intradialytic heparin is minimised during a two-week run-in period using a standardised protocol based on a visual clotting score. Patients still requiring intradialytic heparin after the run-in period are randomised to two weeks of HD with AD followed by two weeks of CD (Sequence 1) or two weeks of HD with CD followed by two weeks of AD (Sequence 2). The primary outcome is the change in CHD with CD compared with AD. Secondary outcomes include metabolic and haemodynamic parameters, and dialysis adequacy.

**Discussion:**

This randomised controlled trial will determine the impact of CD compared with AD on CHD during HD.

**Trial registration:**

ClinicalTrials.gov NCT01466959

## Background

During haemodialysis (HD), blood is exposed to an extracorporeal circuit which activates thrombogenic pathways and clotting [1]. Clotting in the dialysis circuit decreases HD efficiency, and increases nursing workload and costs [2]. Even subclinical clotting of the dialysis circuit may reduce effective dialyser surface area and pore size, decreasing both small and middle solute clearance. Additionally, activation of the coagulation pathway in HD patients may be associated with increased inflammation and accelerated atherosclerosis [3].

In North America, unfractionated heparin is the most common anticoagulant used to prevent clotting during HD [4, 5]. Although effective and inexpensive, it has a narrow therapeutic window without adverse bleeding. Since heparin provides systemic anticoagulation, it is contraindicated in the setting of active bleeding, trauma, pericarditis, intracerebral haemorrhage, thrombocytopenia, coagulopathy, and peri-operative care [6–9]. Furthermore, heparin may lead to osteoporosis, dyslipidaemia, hyperkalaemia, and immune-mediated heparin-induced thrombocytopenia [2, 10–16].

An alternative to systemic heparin anticoagulation for HD is citrate dialysate (CD). CD contains a small amount of citric acid rather than acetic acid as the acidifying agent, at one-fifth the concentration of citric acid used for regional citrate anticoagulation. There are several observational studies [17–27] and two randomised trials using CD in HD patients [28, 29]. These studies demonstrate that CD is associated with decreased clotting of the haemodialysis circuit [17], decreased need for anticoagulation [24, 26, 29], increased dialyser reuse [19], and increased small and middle solute clearance [18–20, 26–28, 30]. These benefits are from an anticoagulation effect that is limited to the extracorporeal circuit without systemic coagulation activation [28]. Other associated benefits of CD include decreased acidosis [18, 22, 28], decreased inflammation [27], decreased oxidative stress [25], improved anaemia [22], improved nutrition [22], and greater haemodynamic stability [21, 28, 31]. CD is well tolerated with no unstable metabolic parameters and no documented adverse effects [18, 22, 29], even in paediatric patients with acute kidney injury [32], in critically ill patients [17], and patients with advanced liver failure [33].

We describe our protocol for a six-week, double-blinded, randomised cross-over trial that investigates whether CD results in reduced cumulative heparin dose (CHD) compared to acetate dialysate (AD) in chronic HD patients. Secondary outcomes address safety concerns, and include metabolic and haemodynamic parameters, and dialysis adequacy.

## Methods

### Study setting

This randomised crossover clinical trial is performed within three community HD units in Calgary, Alberta, Canada, where unfractionated heparin is used for standard intradialytic anticoagulation. All participants provide written informed consent. The study protocol is approved by the Conjoint Health Research Ethics Board at the University of Calgary, and is conducted in accordance with the Declaration of Helsinki (ClinicalTrials.gov, NCT01466959).

### Study population

Eligible patients are ≥ 18 years, and on outpatient conventional HD three times per week for at least three months. Exclusion criteria include: contraindication to heparin, heparin-free HD, known clotting disorder, warfarin therapy, dialysing with a dysfunctional central venous catheter (blood flow rate consistently < 300 mL/min and/or frequent use of thrombolytic), vascular access dysfunction, planned vascular access conversion or procedure during the study period, use of high calcium dialysate, active medical issue, planned kidney transplant during the study period, planned conversion of dialysis modality (peritoneal dialysis, nocturnal dialysis) during the study period, or inability to provide informed consent. Patients with recent modifications to their erythropoiesis-stimulating agent dose are reviewed by the investigator for eligibility.

### Study protocol

After enrolment, each patient’s dose of intradialytic heparin is minimised during a two-week run-in period (Fig. 1) using study protocol (Table 1) which is based on a standardised visual clotting score [34]. The visual clotting score is quantified by inspecting the venous chamber and all four quadrants of the dialyser at the end of the HD session (0: clear dialyser/no clots; 1: few strands/small clots; 2: half clotted; 3: three-quarters clotted; 4: completely clotted, unable to return blood) (Table 1). The heparin dose is reduced to reach a target visual clotting score of 2, then increased slightly and maintained, to achieve the lowest possible dose required to prevent clotting (Table 1). The CHD during the last HD session of the run-in period is considered to be the patient’s baseline heparin dose. Patients still requiring intradialytic heparin after the two-week run-in period, and who still meet inclusion and exclusion criteria, are randomised to one of two treatment sequences (Fig. 1). For sequence 1, patients undergo six HD sessions over two weeks with AD (control), followed by six HD sessions over two weeks with CD (intervention). For sequence 2, patients undergo six HD sessions over two weeks with CD (intervention), followed by two weeks of AD (control) (Fig. 1). Patients begin each study phase (AD and CD) with their baseline intradialytic heparin dose, determined at the end of the run-in period. Nurses subsequently adjust intradialytic heparin dose per protocol (Table 1) during each HD session of each study phase. At the end of the first study phase (two weeks), a 68-h washout period ensures no potential for a carry-over effect. After the wash-out period, patients cross-over to the other treatment for the next two weeks beginning again with their baseline heparin dose (Fig. 1). A two-week duration for each strategy is chosen to ensure adequate time to attain the minimum required heparin dose.

**Fig. 1 Fig1:**
[figure not shown]
Study Flow Diagram

**Table 1 Tab1:** Visual Clotting Score and Heparin Protocol

Clotting Score	Dialyser/Venous Chamber Appearance (at the end of each HD session)	Heparin Dose Adjustment (for the next HD session)
0	Clear	Decrease^a^ boost by 200 units *and* decrease running dose by 200 units/h
1	Few strands/small clot	Decrease^a^ boost by 200 units *and* decrease running dose by 200 units/h
2	½ clotted	Increase boost by 200 units *and* increase running dose by 200 units/h and *maintain* this new heparin dose for the remainder of this study phase only.
3	¾ clotted (able to return blood)	Increase boost by 300 units *and* increase running dose by 300 units/h
4	Completely clotted (unable to return blood)	Increase boost by 400 units *and* increase running dose by 400 units/h

*HD* haemodialysis

NOTE

1) If there is unusually prolonged bleeding from vascular access sites post-HD, for the next HD session, decrease^a^ heparin running dose by 200 units/h and turn heparin off 30 min earlier than usual

2) If there is a discrepancy in score between the dialyser and the venous chamber, the heparin dose adjustment is based on the dialyser clotting score

^a^The minimum possible heparin boost and running dose are 500 units (boost) and 500 units/h. If the heparin dose is to be decreased to less than 500 units (boost and/or running dose) for the next HD session, discontinue the boost and/or the running dose

Randomisation is determined by a computer generated random number list and concealed in sequentially numbered, opaque, sealed envelopes to ensure allocation concealment. Following informed consent and enrolment, the envelope containing allocation sequence is provided to the research coordinator who implements the sequence assignment according to protocol. The intervention and control dialysates, CD and AD, are packaged identically by the manufacturer (Chief Medical Supplies, Ltd., Calgary, Alberta, Canada) for blinding of investigators, patients, and health care staff. All data is confidential, and entered into electronic records by an independent data entry clerk who is blinded to patient allocation.

All study patients are dialysed using Gambro Phoenix® dialysis systems (Gambro-Hospal, Mirandola, Italy) at least three times per week. Each patient’s target weight and dialysis prescription are optimised at the study start by the rounding nephrologist using clinical assessment. Standard dialysis prescriptions (blood flow rate 300–450 mL/min, dialysate flow rate 500 mL/min, dialysate temperature 0.5 °C less than patient temperature, dialysate sodium 137 mmol/L) are maintained unless otherwise prescribed. Dialysers are high-flux, polysulfone (REXEED™, Asahi Kasei Medical Co. Ltd., Tokyo, Japan). HD prescriptions, target weights, and antihypertensive medications are not changed during the study period. The intervention dialysate, CD, contains 2.4 mEq/L of citric acid (Citrasate®, Advanced Renal Technologies, Bellevue, WA), and the control dialysate, AD, contains 4 mmol/L of acetic acid.

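### Table 1 stops heparin reduction after a clotting score of 2 but not after a 3 or 4, so a patient can be taken back to a dose, or to no heparin, that severely clotted

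*Protocol article*

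**What the plan says.** The Study protocol section states the aim of the titration: "The heparin dose is reduced to reach a target visual clotting score of 2, then increased slightly and maintained". The purpose given is the lowest dose that prevents clotting.

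Table 1 turns this into steps after every session:

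- Score 0 or 1: boost down 200 units and running dose down 200 units/h.
- Score 2: both up 200, with the instruction to "maintain* this new heparin dose for the remainder of this study phase only".
- Score 3: "Increase boost by 300 units *and* increase running dose by 300 units/h", with nothing further.
- Score 4: "Increase boost by 400 units *and* increase running dose by 400 units/h", with nothing further.

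Footnote a sets a minimum of 500 units for the boost and 500 units/h for the running dose. It begins "If the heparin dose is to be decreased to less than 500 units (boost and/or running dose" and goes on to say that the component is then discontinued. Neither the table nor the footnote says how heparin restarts after that.

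Two other rules use the resulting doses. On baseline, "The CHD during the last HD session of the run-in period is considered to be the patient’s baseline heparin dose", and "Patients begin each study phase (AD and CD) with their baseline intradialytic heparin dose, determined at the end of the run-in period". Under Cumulative heparin dose (CHD), the primary outcome uses the mean CHD of the last two of the six sessions in each phase.

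**The concern.** The mildest failure ends dose reduction for the phase, while the two worse failures do not. A patient whose score jumps from 0 or 1 straight to 3 or 4 gets an increase, and the next clear session starts the reduction again. Unless a score of 2 happens to occur on the way down, the dose heads back to a level already known to clot the circuit. For that patient no dose is maintained and clotting is not prevented, which conflicts with the aim in the Study protocol section.

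Two things are at stake. The first is repeat exposure to severe circuit clotting within a two-week phase. The second is noise in a trial planned for 20 patients: a dose that cycles has no settled value for sessions 5 and 6 to capture, and a run-in that cycles gives a baseline that depends on where session 6 happens to fall.

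**Working it through.** The plan has no figure of its own on this point, so the check is to run Table 1 as a rule over six sessions.

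**Inputs from the documents.** Steps of -200, +200 (held), +300 and +400; floor 500; six sessions; outcome from sessions 5 and 6; baseline from run-in session 6.

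**Assumptions.** Boost and hourly rate are numerically equal and heparin runs for 4 h, so CHD = boost + 4 x rate = 5 x rate.

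**Step arithmetic (needs no assumption).** After a 4 and two clear sessions: +400 - 200 - 200 = 0. After a 3 and two clear sessions: +300 - 200 - 200 = -100. At the floor one step is enough: 600 - 200 = 400 < 500, so heparin stops.

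**Away from the floor.** Assume 700 units/h or less clots and anything higher runs clear.

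| Start | Score when it clots | Rate in sessions 1 to 6 |
|---|---|---|
| 900 | 2 | 900, 700, 900, 900, 900, 900 |
| 900 | 3 | 900, 700, 1000, 800, 600, 900 |
| 900 | 4 | 900, 700, 1100, 900, 700, 1100 |
| 1100 | 4 | 1100, 900, 700, 1100, 900, 700 |

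The last two rows describe the same clotting threshold. If they were run-ins, baseline CHD would be 5 x 1100 = 5500 in one and 5 x 700 = 3500 in the other, only because the start differed.

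**At the floor.** Assume no heparin scores 3 and every non-zero dose runs clear. Table 1 allows three readings of the restart from zero:

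- Restart at the 500 minimum: 500, 0, 500, 0, 500, 0. The session 5-6 mean CHD is 5 x 250 = 1250, against 2500 if 500 were held.
- Add the increment to zero literally: 500, 0, 300, 0, 300, 0.
- Add the increment to the last non-zero dose: 500, 0, 800, 600, 0, 900. The session 5-6 mean is 5 x 450 = 2250. A start at 600 gives 600, 0, 900, 700, 500, 0, with mean 5 x 250 = 1250.

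All three return to no heparin within the phase.

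**Simulation.** Need is normal with mean 600 and SD 180 units/h, clipped to 100-1200. This matches the CHD of 3000 (SD 900) in Sample size calculations, since 5 x 600 = 3000 and 5 x 180 = 900; using that figure as the minimised need is an assumption. Run-in starts 0 to 400 units/h above need (minimum 500). Shortfalls up to 50, 100 or 200 units/h score 2, the next 200 score 3, and beyond that score 4. Session noise has SD 50 or 100 units/h. This gives six cells of 40,000 patients, compared among those with a non-zero baseline under both rules. The hold rule is the one proposed under fix.

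| Setting | Measure | Table 1 now | With hold |
|---|---|---|---|
| Restart at 500, need 30% lower on citrate | SD of within-patient difference | 1056-1336 | 579-823 |
| Same | Severe clots per citrate phase | 1.24-1.89 | 0.72-1.13 |
| Restart at 500, no effect | SD of within-patient difference | 733-1278 | 453-713 |
| Same | Severe clots per phase | 0.48-1.74 | 0.28-1.25 |
| Literal restart, need 30% lower on citrate | Severe clots per citrate phase | 1.06-1.94 | 0.80-1.40 |

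The within-patient SD also falls under the literal restart, and both measures fall when the increment is added to the last non-zero dose.

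**Mean contrast, need 30% lower on citrate.**

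| Restart reading | Need difference | Now | With hold |
|---|---|---|---|
| At 500 | 935-978 | 1251-1527 | 858-980 |
| Literal | 909-953 | 1040-1143 | 952-1007 |
| Last non-zero dose | 939-967 | 541-704 | 475-559 |

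The first two readings overstate the need difference and the third understates it.

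**The case against.** A reader might infer that the missing hold biases the trial towards citrate: if citrate lowers the need for heparin, more citrate phases reach no heparin, and a session that clotted on zero units counts as heparin saved. Under a restart at 500 that happens. But Table 1 does not state that restart. If the increment is added to the last non-zero dose, the contrast is understated and the hold lowers it further. Nor does the hold always improve the ratio of mean contrast to its SD: under this third reading with a score 2 band of 200 units/h it went from 0.87 to 0.79 in one cell and stayed at 0.65 in the other. Away from the floor (need difference 1650) the contrast is 1640-1774 now and 1697-1856 with the hold, so the hold does not bring it closer there. This objection stands, and the directional claim is not made. The outcome is also defined as heparin received, not as a latent need, so need difference is only a yardstick.

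The size also depends on how often scores skip 2, which the documents do not give. With a score 2 band of 400 units/h and literal restart, the two rules barely differ (contrast 1216-1290 now, 1200-1287 with the hold).

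A further inference would be that a run-in ending on no heparin leaves percent change from baseline undefined. The protocol randomises "Patients still requiring intradialytic heparin after the two-week run-in period", so such a patient might instead be excluded. The text does not settle which.

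Finally, lowering the dose again after an overshoot is a fair way to look for the lowest possible dose, and one severe clot may have another cause; the Discussion mentions access stenosis in a cited study. That is a real cost of a hold. But the plan already accepts a permanent hold after a single score of 2, so extending it to worse scores brings in no new principle.

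**Conclusion.** The gap follows directly from Table 1. After a score of 3 or 4 the dose can return to, or below, one that severely clotted, and near the floor to no heparin. For the patients concerned this defeats the stated aim and leaves the session 5-6 mean and the run-in baseline dependent on the position in the cycle.

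The step arithmetic rests on nothing outside the table. The effects on clot counts and SD rest on assumed score bands, noise, infusion time and need distribution. Their direction is the same under all three restart readings for score 2 bands of 50 to 200 units/h, and the difference almost vanishes with literal restart and a 400-unit band. How many trial patients would be affected is unknown. The direction of any error in the citrate-acetate contrast cannot be determined from the document. This is a cheap improvement worth making, not a demonstrated bias.

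**What to change.** Add to the score 3 and score 4 rows of Table 1: after this increase, do not lower the boost or the running dose again in this phase (run-in included) to or below a dose, including no heparin, that scored 3 or 4; if the next step would do so, maintain the current dose for the rest of the phase. A later score of 3 or 4 still triggers the increase.

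In the examples above (start 900, clots at 700), score 4 then gives 900, 700, 1100, 900, 900, 900 and score 3 gives 900, 700, 1000, 800, 800, 800. At the floor with restart at 500, the sequence is 500, 0, then 500 held.

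Boost and running dose need separate mention because they can differ. With boost 1000 and 500 units/h (CHD 1000 + 4 x 500 = 3000), restart at 500 and a score of 3 without the infusion, the current table gives CHD 3000, 800, 3100, 900, 3200, 1000. The rule gives 3000, 800, then 3100 held.

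The primary outcome stays as it is. A count, by dialysate, of phases that never reached a hold would show how often this matters.

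Cost: no extra data, but nurses must note the dose that clotted. A one-off clot from another cause may hold the dose above the true minimum, by 100 to 200 units/h away from the floor and by up to one 500-unit step at it.

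### Read literally, Note 2 to Table 1 lets heparin be cut after a session in which blood could not be returned; a one-sentence safety clarification closes the gap

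*Protocol article*

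**What the plan says.** The Study protocol section describes the visual clotting score as "quantified by inspecting the venous chamber and all four quadrants of the dialyser". Titration is meant "to achieve the lowest possible dose required to prevent clotting".

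Table 1 turns the score into the next session's dose. Rows 0 and 1 lower the boost by 200 units and the running dose by 200 units/h. Rows 2, 3 and 4 raise both, by 200, 300 and 400. Blood return separates the top two grades: row 3 carries the words "clotted (able to return blood", and row 4 reads "Completely clotted (unable to return blood". After a score of 2 the nurse raises the dose and keeps "this new heparin dose for the remainder of this study phase only".

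Footnote a sets a floor of 500 units for the boost and 500 units/h for the infusion. If a decrease would go below it, the instruction is, "for the next HD session, discontinue the boost and/or the running dose".

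Note 2 covers disagreement between the two parts of the circuit: "the heparin dose adjustment is based on the dialyser clotting score". Note 1, the only other dosing note, covers prolonged access-site bleeding and also lowers heparin.

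**The concern.** Note 2 presupposes that dialyser and venous chamber can receive different scores, and it settles every difference in favour of the dialyser. One combination then gives a dose change in the wrong direction: chamber 4, with blood not returned, and dialyser 0 or 1. The circuit has been lost, and the written rule gives the patient less heparin next time, or none.

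The stake is patient safety and correct titration: another lost circuit and further blood loss. There is also a limited effect beyond the next session. The Study protocol section states: "The CHD during the last HD session of the run-in period is considered to be" the baseline dose. A wrong cut after an earlier run-in session can therefore lower the dose from which both study phases start.

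**Working it through.** The plan gives no figure for this point, so there is nothing to reproduce. The check traces the rule and converts its steps to units per session.

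**Inputs**
- Dose steps: Table 1, rows 0/1 and 4.
- Floor: Table 1, footnote a (500 units; 500 units/h).
- Cumulative heparin dose (CHD) per session: boost B plus hourly rate R times infused hours h, from the Cumulative heparin dose section.
- Infused hours: not stated. Assumed h = 3 to 4.
- Local mean CHD: 3000 units, from Sample size calculations. This is the usual dose, not the minimised one.

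**1. Direction.** With chamber 4 and dialyser 2 or 3, Note 2 still raises the dose. With chamber 4 and dialyser 0 or 1, it leads to the row 0/1 decrease. Only this combination reverses the direction.

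**2. Boost and rate both 700 or more.**
- Literal rule: -(200 + 200h) = -800 at 3 h, -1000 at 4 h.
- Row 4: +(400 + 400h) = +1600 at 3 h, +2000 at 4 h.
- Gap: 2400 to 3000 units.

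**3. Both between 500 and 699.** Each would fall below 500, so both stop and the next CHD is 0. From B + hR, this covers current doses from 500 + 3 × 500 = 2000 to 699 + 3 × 699 = 2796 at 3 h, and from 500 + 4 × 500 = 2500 to 699 + 4 × 699 = 3495 at 4 h.

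**4. One at 700 or more, the other between 500 and 699.** The first takes its step and the second stops.

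**5. Only one component running.** Footnote a allows this.
- Infusion alone at 700 or more: -200h, i.e. -600 to -800.
- Boost alone at 700 or more: -200.
- Either alone between 500 and 699: it stops, and no heparin remains.

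**6. Illustration at a current CHD of 3000.**

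| Components running | h | Next CHD, literal rule |
|---|---|---|
| Both (B 500-1000, R 625-500) | 4 | 0 if B is below 700; otherwise B - 200 = 500 to 800 |
| Infusion only, R = 750 | 4 | 4 × 550 = 2200 |
| Both (B 500-1500, R 833-500) | 3 | about 700 to 2200, depending on the split |
| Infusion only, R = 1000 | 3 | 3 × 800 = 2400 |
| Boost only, B = 3000 | any | 2800 |

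Holding the dose keeps 3000. With both components running, row 4 gives 4600 at 3 h and 5000 at 4 h.

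**7. When it applies.** It applies only before a score of 2 has fixed the dose for the phase. It does not apply after the last session of the run-in or of a phase: the baseline is the dose given in the last run-in session, and each phase restarts from that baseline.

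**The case against.** The strongest reply is that failed return is a property of the whole circuit. The Study protocol section describes one score from inspecting both parts, and rows 3 and 4 are divided by whether blood could be returned. On that reading a lost circuit is score 4, no discrepancy arises and Note 2 is not triggered. The scoring that sets the dose is done by a single trained research nurse, who may well read it so. This is plausible. But the column grades appearance, Note 2 presupposes separate scores, and nothing says that failed return comes first. Where two readings move the dose in opposite directions, the table should say which applies.

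Second, the event is probably rare. A dialyser holding unreturned blood may seldom look clear, and access dysfunction and known clotting disorders are excluded. This stands, and it limits the weight of the point.

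Third, a journal article condenses the protocol, and a clinical override may exist in the full document. That may be so. The point, however, is not a missing detail but a stated rule without exception that can point the wrong way.

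Fourth, a lost circuit is not always a heparin shortfall. The Discussion mentions a clotting episode related to access stenosis, and the Background stresses heparin's narrow therapeutic window. This stands against making row 4 mandatory. Choosing between row 4 and a hold by a judged cause would also add discretion to a fixed algorithm whose result is the primary outcome. It is no argument for a decrease.

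A reader might infer that the rule biases the comparison of dialysates. The documents do not support this: the rule is the same in both blinded phases, and both start from the same baseline. Nor do they show that a typical patient would lose nearly all heparin. The range of 0 to 800 units at a CHD of 3000 and 4 h needs boost and infusion both running; the single-component states leave 2200 or 2800.

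**Conclusion.** The point holds as a minor safety clarification. The literal wording allows a heparin cut, or a stop of any component that would fall below 500, after a session with failed blood return when the dialyser scores 0 or 1. The sizes in the working describe one patient's next session. They rest on the assumed 3 to 4 h of infusion and on which components are running.

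The documents give no frequency, so no effect at trial level can be estimated, and none is claimed for sample size, alpha or the model. Dialyser primacy for all other discrepancies is a legitimate design choice. Only the bar on a decrease is beyond debate; whether to raise the dose or hold it is for the sponsor.

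**What to change.** Add to Note 2: *A session in which blood could not be returned is never followed by the row 0/1 decrease; unless Note 1 applies, the dose is at least held.* Row 4 may be used instead of a hold if the sponsor fixes that in advance, so that the choice is not made case by case. Keep dialyser primacy for every other discrepancy, and leave Note 1 and the row 2 lock as they are.

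The cost is one sentence. In these rare cases the next session has more heparin than under the literal rule: 800 to 1000 units when both components are at 700 or more, and otherwise whatever the literal rule would have removed. If the sponsor chooses row 4, the next session has 1600 to 2000 units more than a hold when both components are running. Sample size and analysis are unchanged.
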